### Ethics Approval

This study, which will be conducted according to the Declaration of Helsinki, has been approved by the Medical Science Research Ethics Committee of the Peking University Third Hospital (IRB00006761-M2021085) after a careful audit of the design and content.

### Informed Consent and Funding

We will fully inform the patients of the purpose and procedures of this study, as well as their obligations and potential costs and risks. An informed consent form has been drafted and will be signed voluntarily by each participant.

This study is a self-organized project and receives no financial support or funding from any commercial entity. Therefore, conduct of the study, data processing, and interpretation of the results will not be influenced by any commercial entity.

## Results

Study design, ethical review, and research registration have been completed. Enrollment commenced in June 2022, and enrolled patients are being visited regularly. Patient enrollment is expected to be completed by June 2027, and the study results will be submitted for publication in early 2029.

## Discussion

### Expected Findings

We anticipate that the findings of our cohort study will support the use of a surgical treatment strategy for patients with SMLC. Although we understand that a combination of different antitumor therapies, namely comprehensive treatment, is recommended for patients with SMLC, there is no consensus or established guideline on how to practice it. Our study aims to explore surgery-based comprehensive treatment for patients with SMLC. Through this study, we aim to validate our proposed synchronized schedule for a multimodality therapy and eventually hope to establish a survival prediction model.

### Previous Studies

Fundamentally, the primary goals of surgery are to restore spinal stability, relieve pain, and decompress tumor mass squeezing of the spinal cord, if any. Yao et al [20] reviewed studies on spinal metastasis and found that surgery could significantly improve neurological function and quality of life, even for patients with advanced lung cancer. However, we have not yet gained firm evidence on the impact of surgery on patients’ survival, though many papers have reported favorable postoperation outcomes. Truong et al [17] recruited patients with SMLC undergoing surgery and found that 14 (16%) out of 87 patients survived beyond 12 months. Chen et al [23] reported the median survival of their cohort to be 12 months; patients undergoing excisional surgery had a longer survival time than those with palliative surgery. Contrarily, in a systematic review by Armstrong et al [21], the authors reported unfavorable outcomes for surgical intervention, of which a shorter median OS was found in the surgical group compared to the nonsurgical group (7.5 months vs 8.5 months). This result was echoed in Amelot et al’s [24] study. These authors concluded that survival of SMLC depends merely on genotype and neurological and personal status, and scarcely on surgical resection. In the past decade, the combination of separation surgery and high-dose hypofractionated SBRT has emerged as an effective option for spinal metastasis, including SMLC [18]. The core principle of this procedure is to circumferentially remove the tumor mass encasing the spinal cord and create a safe zone between the cord and the tumor (≥3mm) for the subsequent delivery of radiation treatment [9,25,26].

As our understanding of the molecular biology of lung cancer increases, many mutated targets are being identified, including the epidermal growth factor receptor (EGFR), anaplastic lymphoma kinase, ROS1, BRAF V600E mutation, etc [6,7,27,28]. Targeted drugs can act directly on these specific mutations and diminish tumor cells. Dohzono et al [29] compared the median OS of patients with SMLC receiving or not receiving EGFR tyrosine kinase inhibitors and found the former group enjoyed a longer OS period (21.4 months vs 6.1 months). In recent years, the application of some immunotherapeutic drugs has proven to be effective [7]. The concept of immunotherapy is to introduce specific blockers to inhibit some immunological signaling paths that are related to the development and metastasis of tumors. Currently, anti-PD-1 and anti-PD-L1 antibodies have been recognized as the choice of care for some advanced lung cancers after the failure of first-line cytotoxic therapy [30]. Borghaei et al [28] found that the median OS period of PD-L1(+) patients who received specific targeted blockers was longer than that of PD-L1(–) patients (17.7 months vs 10.5 months). Furthermore, systematic use of bone-targeted agents (eg, bisphosphonates and denosumab) has significantly reduced devastating spinal-related events, such as paralysis and loss of self-care ability [31].

### Strengths and Limitations

The main strength of our study is that it is the first research project to examine the feasibility and outcomes of synchronized adjuvant therapies after surgical intervention for SMLC in a prospective cohort and using a more scientific methodology. This methodological merit will strongly empower the justification for using positive yet invasive treatment modalities instead of conventional palliative care in patients with SMLC. Second, for the purpose of rapid recovery, we are starting rehabilitative intervention at an early stage after surgery. In addition, we recognize the importance of starting adjuvant therapies early after surgery, and this practice will be implemented and examined in our clinical trial.

There are some potential biases in this study that might compromise the reliability and accuracy of the results, but we have designed some solutions to reduce bias. First, though it is difficult to blind the intervention providers and patients, outcome assessors and data processors will be blinded. Second, during the follow-ups, we will encourage face-to-face interviews, but online interviews will also be accepted, considering the possible emergence of scenarios like a COVID-19 surge, in order to reduce the rate of dropout.

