#### Secondary Outcomes

Secondary outcomes include the following:

The progress-free survival period, defined as the time after the start of antitumor therapies until disease progression.Recovery of SMLC-related symptoms, defined as the relief of locoregional pain, which is measured by visual analogue scale (VAS) values, and the recovery of neurological status, which is assessed using the American Spinal Injury Association (ASIA) score. Immediate improvement in VAS and ASIA scores is assessed before discharge.Recovery of self-care performance, assessed using the Karnofsky Performance Scale (KPS) score and the Eastern Cooperative Oncology Group (ECOG) performance score.Quality of daily life, assessed by the Short Form 36 Health Survey Questionnaire.

Other outcomes for evaluation include complications in antitumor treatment. Surgical complications are rated according to the system proposed by Clavien et al [22], whereas toxicity of radiotherapy and antitumor drugs is graded using the National Cancer Institute’s Common Toxicity Criteria for Adverse Events (version 5.0). The endpoint of the study is the death of the recruited patient. The primary outcome is assessed by the endpoint of the study, whereas secondary and other outcome metrics are assessed at each visit.

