### Data Management and Supervision

We will assign a specific investigation team to assess outcomes and process the data, and train the team in this regard. In addition, we will formulate some basic rules for the process of patient follow-up; outcomes assessment; and data entry, coding, and storage, namely double assessment, dual entry, and checks by independent investigators. Outcome assessors will be blinded to the patients’ intervention allocation. Our institute’s scientific research supervising team, which excludes all investigators in this study, will monitor the study process, data safety and authenticity, and occurrence of adverse events.

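### Blinded outcome assessment is claimed without exception, but it cannot hold for surgical complications, cannot protect VAS or SF-36, and is doubtful for the examiner-rated scales and data processing as organised

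*Protocol article*

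**What the plan says.** The Data Management and Supervision section of the protocol article states: "Outcome assessors will be blinded to the patients’ intervention allocation". No outcome is excepted. The same section gives assessment and data handling to one group of staff: "We will assign a specific investigation team to assess outcomes and process the data".

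Strengths and Limitations repeats the claim, extends it to data processors, and lists it first among the measures against bias: "though it is difficult to blind the intervention providers and patients, outcome assessors and data processors will be blinded". The only other measure listed there concerns dropout: "we will encourage face-to-face interviews", with online contact as the alternative.

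Secondary Outcomes names progression-free survival, pain ("the relief of locoregional pain, which is measured by visual analogue scale (VAS) values"), ASIA neurological status, KPS and ECOG, and SF-36. VAS and ASIA are also taken before discharge. The section then adds: "Other outcomes for evaluation include complications in antitumor treatment". Surgical complications are graded on the Clavien system, and toxicity of radiotherapy and drugs on CTCAE version 5.0. All secondary and other outcomes are assessed at each visit.

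**The concern.** Treatment follows clinical indication, and the two groups differ visibly in what is done to them. In that setting, blinded assessment is the only listed protection against biased measurement. It is stated as a general property of the study, yet several of the outcomes either reveal the treatment or are scored by someone who knows it.

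The secondary results are what is at stake. The Discussion names stability, pain relief and decompression as the main goals of surgery, and says firm evidence on survival is lacking. Pain, neurological function and quality of life are therefore where a benefit of surgery is most likely to be argued. The authors also say that they expect the findings to favour a surgical strategy. If pain and quality-of-life results are presented as coming from a blinded assessment, readers will give them more weight than open-label patient ratings can carry, and in the direction the authors expect.

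**Working it through.** The article gives no figure on this point and no arithmetic applies. The check sets each outcome against the blinding statements and asks three questions: who produces the rating, does that person know the treatment, and does the outcome itself reveal the group?

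1. **Surgical complications (Clavien).** These can arise only in the surgical group. Whoever grades one knows the patient was operated on, so the claim cannot hold here.

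2. **VAS pain.** The patient is the rater, and the article concedes that patients are difficult to blind. Masking the person who records the number does not mask the person who chooses it. Even if the recorder is blinded, the outcome is not protected.

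3. **SF-36.** This is a patient-completed questionnaire, so the reasoning for VAS applies.

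4. **ASIA, KPS and ECOG.** These are rated by an examiner, and the scores do not in themselves disclose treatment. A separate rater could be masked. As organised, this is doubtful for three reasons:
   - One team assesses outcomes, surgical complications included, at the same visits.
   - The pre-discharge ASIA assessment falls, for surgical patients, within the operative admission.
   - Later contact is preferably face to face, with patients who know what they received.

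5. **CTCAE toxicity.** The Treatment section gives radiotherapy and antitumor drugs to both groups: SBRT and drugs alongside surgery in one, and locoregional radiotherapy with drugs as a condition of enrolment in the other. Grading such a toxicity does not by itself identify the group.

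6. **Progression.** The article defines the interval but names no method or body site for declaring progression. Imaging appears only among the exposure measures. Whether the reader can be masked cannot be settled from this document.

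7. **Data processing.** The Exposure Measures section lists surgical approach, duration of the operation, blood loss and length of stay after surgery. Most of these fields have content only for operated patients. Anyone who handles the full record can see the group, and the team that assesses outcomes is the one that processes the data.

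8. **All-cause death (primary outcome).** This leaves little room for assessor judgement, so knowledge of treatment matters little to its measurement.

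In sum, the claim cannot hold for item 1 and gives no protection for items 2 and 3. It is doubtful as organised for items 4 and 7. Item 6 is undetermined, item 5 does not in itself break masking, and item 8 scarcely depends on it.

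**The case against.** The strongest reply is that the article condenses a longer protocol. Masking procedures such as separate raters, covered wounds, instructions to patients or central reading are commonly left to that document, so their absence here does not show that masking is impossible. One team need not mean that one person does every assessment, and the article also mentions double assessment and checks by independent investigators. This stands for ASIA, KPS, ECOG and progression, which is why they are called doubtful or undetermined and not refuted. Double assessment and independent checks improve reliability, but they do not in themselves keep anyone unaware of the group. No procedure in a fuller document could mask the grader of a surgical complication or the patient who rates pain.

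Second, the sentence that claims blinding also admits that patients are hard to blind, so a careful reader can discount VAS and SF-36. That is true, but the sentence still presents assessor blinding as the solution and does not say which outcomes it leaves uncovered.

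Third, surgical complications occur in one group only, so there is no between-group comparison of them for an unblinded grader to distort. This also stands. For complications the error lies mainly in the description. The consequence for treatment comparisons falls chiefly on VAS and SF-36, and on the examiner-rated scales if their raters are not masked.

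A reader might go further and infer that blinding is impossible for every outcome except death. The document does not support that. The examiner-rated scales could be masked, toxicity grading applies to both groups, and nothing is said about how progression is read. Visible scars, or postoperative change on scans, are plausible routes of unmasking but are not stated in the text.

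**Conclusion.** The unqualified claim is wrong for surgical complications and offers no protection for VAS and SF-36. It is doubtful for ASIA, KPS, ECOG and data processing as the article describes their organisation. The consequence is confined to secondary and other outcomes. No bias can be sized from the document, and none is asserted.

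The conclusion rests on two premises: that VAS and SF-36 are scored by the patient, and that patients know whether they had surgery, which the article in effect concedes. The doubtful items rest on the article's account of one team, its visits and its data fields. A fuller protocol that describes separate masked raters or a coded dataset would resolve them.

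A reader might also infer that claims of benefit should therefore rest on overall survival alone. That does not follow. Death is robust to assessor knowledge, but patients are assigned to surgery for refractory pain, worsening neurology or spinal instability, so the survival comparison remains open to confounding by indication.

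**What to change.** Qualify the statements in Data Management and Supervision and in Strengths and Limitations as follows:

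- Describe VAS, SF-36 and surgical complications as open-label, and interpret them so in the results.
- Claim blinding for ASIA, KPS, ECOG and progression only where the rater or reader is actually kept unaware of the group. Otherwise report these as open-label too.
- Claim blinded data processing only where it is real, for example where the analyst works from a coded dataset without the surgery-only fields.
- Say that all-cause death is little affected by assessor knowledge, and that this does not address confounding by indication.

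The minimum change is wording and leaves the primary outcome and its analysis as they are. Separate masked raters or a coded dataset would need some organisation, but only if the study wishes to keep the claim for those items. The downside is that the study gives up part of a methodological strength it now claims.

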### Conclusions

We present the protocol for a prospective cohort study of patients with SMLC. Through this study, we will explore the outcomes of surgery-based comprehensive treatment. In addition, we will also investigate prognostic factors of SMLC and provide references for peer surgeons.

## Appendix

Multimedia Appendix 1 The visit timeline and list of tasks.

## Abbreviations

ASIA: American Spinal Injury Association
C-index: concordance index
ECOG: Eastern Cooperative Oncology Group
EGFR: epidermal growth factor receptor
KPS: Karnofsky Performance Scale
OS: overall survival
SBRT: stereotactic body radiotherapy
SMLC: spinal metastases of lung cancer
VAS: visual analogue scale
